## Abstract

**Background:**

Primary percutaneous coronary intervention (PCI) for patients presenting with acute myocardial infarction (AMI) caused by left main coronary artery occlusion is associated with significantly higher mortality and risks of major adverse cardiovascular events. Deferred stent implantation may improve prognosis of primary PCI by reducing distal embolization and no-reflow phenomenon. There is no randomized clinical trial focusing on the effect and outcome of deferred stent implantation on primary PCI for left main coronary artery occlusion in contrast with conventional strategy.

**Methods:**

The Optimal Strategy of Primary Percutaneous Coronary Intervention for Acute Myocardial Infarction due to Unprotected Left Main Coronary Artery Occlusion (OPTIMAL) study (ClinicalTrials.gov Identifier: NCT03282773) is an open-label, randomized, multicenter clinical trial in which 480 patients presenting with AMI caused by left main coronary artery occlusion recruited from 30 hospitals in mainland China will be randomly assigned 1:1 to immediate stenting or deferred stenting (scheduled 4–10 days after primary angioplasty) groups. The primary endpoint is a composite of all-cause mortality or recurrent myocardial infarction at 30 days after randomization. The secondary outcomes include all-cause mortality, cardiac death, recurrent myocardial infarction, and unplanned target vessel revascularization at 30 days, 6 months, and 12 months.

**Discussion:**

The OPTIMAL study is designed to compare the clinical performance of deferred stenting with that of immediate stenting for AMI caused by left main coronary artery occlusion.

**Trial registration:**

ClinicalTrials.gov Identifier: NCT03282773. Registered on 10 September 2017.

**Electronic supplementary material:**

The online version of this article (10.1186/s13063-019-3211-0) contains supplementary material, which is available to authorized users.

## Background

Of all patients with acute myocardial infarction (AMI), 4–7% have a culprit lesion in the left main coronary artery whose abrupt occlusion triggers ischemia and myocardial infarction (MI) [1, 2]. Unprotected left main coronary artery occlusion–induced AMI (LM-AMI) often presents with cardiogenic shock and is associated with higher risks of major cardiac adverse events and higher mortality even if treated with reperfusion therapy in time [3, 4]. Coronary artery bypass graft (CABG) is recognized as the standard revascularization strategy for this situation [5, 6]. Nonetheless, although CABG is recommended by the guidelines, it still carries very high mortality in patients with LM-AMI. Percutaneous coronary intervention (PCI) for LM-AMI was revealed to have a clinical outcome comparable to that of CABG in recent studies because of the application of second-generation drug-eluting stents and improvement of PCI procedure [7]. Primary PCI (PPCI) for LM-AMI is an alternative revascularization strategy to CABG for selected patients.

Stents are immediately implanted in conventional PPCI after successful revascularization, and 12–30% of patients underwent immediate stenting have not achieved thrombolysis in myocardial infarction (TIMI) grade 3 flow, which usually indicates impaired perfusion and unfavorable clinical outcome [8]. Impaired perfusion or no-reflow phenomenon, partly explained by distal embolization and microvascular obstruction caused by stent implantation, may induce increased infarct area, reduced ventricular function, and poor prognosis [9]. In addition, no-reflow–triggered ischemia reperfusion injury after immediate stenting may cause ventricular arrhythmia, myocardial stunning, and even sudden death [10, 11]. Deferred stent implantation, as an alternative strategy, can attenuate distal embolization and reperfusion injury since enhanced anti-thrombotic therapies and myocardial preconditioning of oxidative stress can be applied during the delayed period. On the other hand, deferred stent implantation provides doctors with time to apply anti-thrombotic therapy to alleviate thrombus burden and optimize stent implantation. The efficacy of deferred stenting was supported by some studies with improved peri-procedure outcome and potential favorable long-term prognosis [12–16]. In contrast, several studies, including three randomized controlled trials (RCTs), failed to prove the advantage of delayed stenting and even led to controversial conclusions [17–19]. Further investigation is necessary to evaluate the safety and efficacy of deferred stent implantation for LM-AMI. Therefore, the present study is aimed to compare deferred stent implantation with conventional procedure and optimize the standard PCI procedure for patients with LM-AMI.

## Methods

### Objectives and study design

The aim of this open-label, multicenter RCT is to compare immediate stenting with deferred stenting for LM-AMI in 30 hospitals in China. We hypothesize that patients with LM-AMI receiving deferred stent implantation will have improved short-term and long-term clinical outcomes compared with those receiving immediate stenting. A total of 480 patients with diagnosed LM-AMI will be randomly assigned in a 1:1 ratio to either deferred stenting or immediate stenting and followed for up to 12 months.

### Recruitment

Patients with LM-AMI will be consecutively enrolled from 30 clinical centers in China. We recruited participating centers on a voluntary basis. Four centers were not included in the trial, because the numbers of PPCI per year in these centers were less than 50 and they may not have enough experience in treating LM-AMI. The participating centers are located mostly in southern China (20 out of 30) while several other hospitals (10 out of 30) from northern districts are also involved (Additional file 1: Table S1). Most of them are third-grade class-A hospitals (25 out of 30). All participating centers can perform PPCI in 24 h, 7 days a week, and had a minimum volume of 500 PCI procedures and 50 PPCI procedures annually. Coronary care unit and surgery backup are available in all of the centers involved. Additionally, chest pain centers and quick-reaction systems of PCI for patients with AMI have been established among all of these centers. The study protocol and documents have been distributed to the investigators of each center. The OPTIMAL (Optimal Strategy of Primary Percutaneous Coronary Intervention for Acute Myocardial Infarction due to Unprotected Left Main Coronary Artery Occlusion) staff of physicians completing the protocol are responsible for online training and problem solving. Recruitment started on November 1, 2017 and will terminate when the estimated number of patients is reached and we estimate that this will take 3-4 years. Patients are eligible for enrollment if AMI is diagnosed within 12 h and primary angiography shows left main coronary artery occlusion and they reach TIMI 3 flow after reperfusion treatment of balloon dilatation or optional thrombus aspiration or both (Table 1) [20]. Patients with AMI including ST-segment elevation myocardial infarction (STEMI) and non-ST-segment elevation myocardial infarction (NSTEMI) will be enrolled in the study because a certain number of patients with left main coronary artery occlusion present with NSTEMI instead of STEMI. Patients who are more than 80 years old and have malignant tumor, end-stage organ failure, or other terminal diseases are excluded from the study for their shorter life expectancy, more clinical complications, and less availability to complete the follow-up. In addition, patients who cannot tolerate PPCI and anti-platelet therapy or who are included in other ongoing trials will not be eligible. Both peri-procedural and long-term outcomes will be recorded in the 12-month follow-up. Written informed consent is obtained before primary angiography.

**Table 1 Tab1:** Eligible criteria

Inclusion criteria	
• 18 years old ≤ age ≤ 80 years old	
• Clinical diagnosis of acute myocardial infarction (AMI) occurred within 12 h^a^	
• Left main coronary artery occlusion—thrombolysis in myocardial infarction (TIMI flow 0, 1, or 2)—confirmed by primary angiography	
• TIMI flow grade 3 achieved after interventional pretreatment such as thrombus aspiration and balloon dilatation	
Exclusion criteria	
• Life expectancy less than 1 year^b^	
• Contraindications to aspirin or other anti-platelet drugs	
• Patients who are included in other ongoing trials	
• Pregnant	
• Patients unable or unwilling to sign the informed consent form	

^a^AMI is defined in accordance with the *Third Universal Definition of Myocardial Infarction* [20]

^b^Life expectancy here is the mean number of years of life remaining, which is estimated through the medical history and clinical parameters by the investigators of each center. This criterion is suitable only for patients who have a malignant tumor, end-stage organ failure or other terminal diseases. Patients with medical history of these terminal diseases and life expectancies assessed by specialists of less than 1 year are not eligible

### Randomization

Eligible patients will be randomly assigned 1:1 to immediate stenting or deferred stenting after primary angioplasty and informed consent (Fig. 1). Random allocation sequence has been generated by using a computer-based system before recruitment started, and results are encrypted and uploaded to a network accessible to all research centers routinely in stacks of sealed electronic envelopes that can be uncovered only with passwords when patients are enrolled. The block size is 4. When a patient is eligible in one center, the investigators of that center will download and open the electronic envelope with passwords obtained from the system and get the result of random allocation and will report the information of enrollment in an online research database which will inform all of the other investigators.

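### A single published block size of 4 in an open-label trial weakens allocation concealment: up to one third of allocations could be deduced, depending on two facts the article does not state

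*Protocol article*

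**What the plan says.** Protocol article, Objectives and study design: "The aim of this open-label, multicenter RCT is to compare immediate stenting with deferred stenting". The same section gives the size: "A total of 480 patients with diagnosed LM-AMI will be randomly assigned in a 1:1 ratio".

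Protocol article, Randomization: patients are "randomly assigned 1:1 to immediate stenting or deferred stenting after primary angioplasty and informed consent". The sequence was generated by computer before recruitment, encrypted, and placed in "sealed electronic envelopes that can be uncovered only with passwords when patients are enrolled". On blocking there is one sentence: "The block size is 4". No variation in size is described. After opening the envelope, the centre "will report the information of enrollment in an online research database which will inform all of the other investigators".

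Protocol article, Recruitment: "Patients with LM-AMI will be consecutively enrolled from 30 clinical centers in China", and "The study protocol and documents have been distributed to the investigators of each center".

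Eligibility (Recruitment and Table 1) requires TIMI 3 flow after pretreatment. Under Clinical procedures, patients in whom that flow is not regained are stented at once and left out of the analysis.

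The article does not say whether the list is central or separate for each centre, or whether the report to other investigators names the arm.

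**The concern.** In a 1:1 block of known fixed size, the last allocation always follows from the earlier ones, and sometimes the one before it does too. Encryption and passwords stop an investigator from reading the next allocation. They do not stop anyone from working it out from arms already known. In an open-label trial each centre knows the arms of its own patients, and the block size stands in a public article.

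Foreknowledge matters where enrolment involves judgement. Here the last eligibility step, TIMI 3 flow after pretreatment, is judged locally just before the envelope is opened. An operator who expected one arm and preferred the other could, knowingly or not, let that affect the grading. A patient graded below TIMI 3 then drops out of the comparison. The primary endpoint is death or recurrent infarction within 30 days. The Discussion describes cardiogenic shock as frequent (26%) in left main occlusion, so much of a patient's prognosis is visible before allocation. Selection by severity, even if modest, would bear directly on that endpoint.

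**Working it through.** The article gives no figure for predictability, so there is none to reproduce.

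**Inputs.** Block size 4 and ratio 1:1 (Randomization); 480 patients (Objectives and study design); 30 centres and 3 to 4 years of recruitment (Recruitment).

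**1. Full knowledge of earlier arms in the block.** A block with two of each arm has 6 possible sequences: AABB, ABAB, ABBA, BBAA, BABA, BAAB. An allocation is certain once one arm has been used twice in the block.

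| Position | Certain in | Chance that the best guess is right |
|---|---|---|
| 1 | 0 of 6 | 1/2 |
| 2 | 0 of 6 | 2/3 |
| 3 | 2 of 6 (AABB, BBAA) | 1/3 × 1 + 2/3 × 1/2 = 2/3 |
| 4 | 6 of 6 | 1 |

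- Certain: (0 + 0 + 2 + 6) / 24 = 8/24 = 1/3.
- Over 480 patients: 480 / 3 = 160.
- Per centre: 480 / 30 = 16 patients on average, and 16 / 3 = 5.3 certain allocations.
- Best guess: (1/2 + 2/3 + 2/3 + 1) / 4 = 17/24 = 70.8%, against 50% without blocking.

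**2. When this applies.** It applies (a) if each centre has its own list, because an open-label centre knows its own history, or (b) if there is one central list and the shared report names the arm. Either way, someone must keep track of where blocks begin.

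**3. Central list, arm not in the report.** A centre then knows only its own arms. Assume that each patient comes from any of the 30 centres with equal chance, and that the centre can follow block position.

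- Position 3 is certain if both earlier patients came from the same centre, (1/30)² = 1/900, and had the same arm, 1/3. This gives 1/2700.
- At position 4, exactly one pair among the first three shares an arm. Both must come from the present centre: 1/900 = 3/2700.
- Average over four positions: (0 + 0 + 1/2700 + 3/2700) / 4 = 1/2700 = 0.037%. A simulation gave 0.036%.
- Over 480 patients: 480 / 2700 = 0.18, less than one allocation.

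Uneven recruitment raises this in large centres: for a centre recruiting a fraction f of all patients, the certain share of its own allocations is f²/3.

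**4. Other block schemes, with full history known.** For the mixed schemes, the possible sizes are known and equally likely, but their order is hidden. The mixed rows are simulated.

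| Scheme | Certain | Best guess right |
|---|---|---|
| Fixed 4 | 33.3% | 70.8% |
| Fixed 6 | 25.0% | 68.3% |
| Fixed 8 | 20.0% | 66.6% |
| Mixed 4/6 | about 5% | about 69% |
| Mixed 4/6/8 | about 2% | about 68% |

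Varying the size removes nearly all certain allocations but hardly changes how often a good guess is right.

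**The case against.** The strongest reply is that the one third is a conditional maximum. It needs centre lists or a report that names the arm, and the article describes neither; it speaks only of enrolment information. This stands. On the text alone the certain share may lie anywhere from almost 0% to 33%. A reader might infer that the arm is broadcast to all centres, but the documents do not say so.

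A reader might also infer that concealment fails outright. That is not supported. The sequence was generated in advance, encrypted, and released by password for each patient, and even with full history two thirds of allocations are not certain.

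Third, there are safeguards. Enrolment is stated to be consecutive. Recruitment places consent before primary angiography, although Randomization and Ethical considerations require only that it precede randomization. Core-lab readers are blinded to allocation, and baseline differences by arm can be examined and adjusted for by the planned logistic regression. It would therefore be wrong to say that selection could never be detected or corrected. These safeguards are partial, however. Consecutive enrolment governs eligible patients, and eligibility is the judgement in question. The article does not make core-lab reading a condition of randomization, and it describes data collection for enrolled patients. Adjustment cannot restore patients who were never enrolled or account for unmeasured severity.

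Fourth, exploitation would take effort: at 16 patients per centre over 3 to 4 years, a centre sees about 4 to 5 a year, in emergencies. This makes systematic prediction less likely without ruling it out. Nothing in the article shows that it has happened.

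**Conclusion.** The point holds as a weakness of concealment. A fixed, published block size of 4 in an open-label trial makes up to one third of allocations (about 160 of 480) deducible with certainty and lifts best-guess accuracy to as much as 71%. Both figures assume that block position is tracked, and that either lists are by centre or the shared report shows the arm. With one central list and no arm in the report, the certain share is about 0.04% under equal recruitment across centres.

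The arithmetic is exact; which case applies cannot be settled from the article. The local TIMI 3 judgement immediately before allocation gives foreknowledge a route into enrolment, and blinded core-lab reading and baseline comparison would reveal selection only in part. The change is inexpensive and worth making whichever case applies.

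**What to change.** For the part of the list not yet used:

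1. Regenerate it with randomly varying block sizes, for example 4, 6 and 8, and do not disclose the sizes to centres.
2. Leave the allocated arm out of reports to other investigators.
3. Record the post-pretreatment TIMI grade in the database before the password is released. This helps most if it is done for every patient who reaches that step, so that those not randomized also leave a record.

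All three are needed, because mixed blocks leave best-guess accuracy at about 68%. Item 2 protects against prediction only under a central list; with centre lists each centre knows its own arms anyway, and items 1 and 3 carry the weight. In either case, the sponsor should state whether lists are by centre and whether the shared report shows the arm.

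The cost is a new list for the remaining patients, a change in database permissions and one locked field. The statistical downside is a slightly larger possible imbalance between arms.

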**Fig. 1 Fig1:**
[figure not shown]
OPTIMAL study design flowchart. Abbreviations: *AMI* acute myocardial infarction, *OPTIMAL* Optimal Strategy of Primary Percutaneous Coronary Intervention for Acute Myocardial Infarction due to Unprotected Left Main Coronary Artery Occlusion

### Clinical procedures

PCI procedures are performed in accordance with each clinical center’s standard routines. There are no restrictions on the balloons, guide wires, thrombus aspiration, or intra-aortic balloon pump usage. The choice of transradial or transfemoral approach will be determined by the operator. We recommend that the participating centers apply the minimalist immediate mechanical intervention (MIMI) technique with small balloon dilatation and thrombus aspiration for the pretreatment. New-generation drug-eluting stents are applied in all participating centers, and the exact type and size of the stents are possibly different. For immediate stenting, stents are implanted immediately after blood flow is regained by interventional pretreatment. Deferred stenting is scheduled 4–15 days after primary angioplasty and in the same hospitalization period. Immediate stenting will be applied if TIMI grade 3 flow cannot be retrieved and these cases will not be enrolled in analysis. CABG is considered as an alternative and will be scheduled within 6 h after PCI procedure failure. For the deferred stenting group, stent implantation will be canceled at the operator’s discretion if the patient is unsuitable for deferred stenting or stent implantation is unnecessary during the second PCI. These patients will be excluded from the per-protocol set but will still be in the intention-to-treat set.

All patients will be transferred to the coronary care unit after the primary angiographic procedure. Intravenous glycoprotein IIb/IIIa inhibitor will be maintained for 18–36 h after PPCI. A loading dose of aspirin and P2Y12 inhibitors will be given before the procedure. An intravenous bolus of unfractionated heparin (100 U/kg) will be administrated right before the procedure to achieve therapeutic activated clotting time. Dual-anti-platelet therapy will be maintained during the deferred period and for at least 1 year after PCI. The peri-procedural treatment is in accordance with the Chinese guidelines for the management of AMI [21].

### Sample size

The annual primary outcome event rate is 22.9%, which we estimated through integrating results of several observational trials [7, 22–26]. Because research data about stent implantation in patients with LM-AMI cannot be found, we have to use the data from other trials that enrolled only a few patients with LM-AMI. According to the results of the OPTIMAL study and the experience of our center, we determined a 35% relative decrease in primary outcome, which is conservative given the high mortality and incidence of adverse events for LM-AMI [15]. The study planned to enroll 240 patients for each arm given a 10% rate of loss (two-sided alpha of 0.05 and 80% power to demonstrate the relative decrease).

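### The stated inputs need about 416 patients per arm, not 240; as planned, power is about 57% rather than 80%

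*Protocol article*

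**What the plan says.** The Sample size section of the protocol article gives every input to the calculation and its result.

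- Event rate: "The annual primary outcome event rate is 22.9%, which we estimated through integrating results of several observational trials".
- Effect: "we determined a 35% relative decrease in primary outcome, which is conservative given the high mortality and incidence of adverse events".
- Error rates: "two-sided alpha of 0.05 and 80% power to demonstrate the relative decrease".
- Result: "The study planned to enroll 240 patients for each arm given a 10% rate of loss (two-sided alpha of 0.05 and 80% power" to show that decrease).

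Objectives and study design confirms the total and the allocation: "A total of 480 patients with diagnosed LM-AMI will be randomly assigned in a 1:1 ratio to either deferred stenting or immediate stenting". Statistical analyses compares outcomes by chi-squared or Fisher exact test, so a two-proportion calculation is the matching one. No formula is given, and no second event rate appears anywhere in the article.

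**The concern.** An 8-point difference around a mean rate of 19% is a modest contrast, and 216 evaluable patients per arm looks too few to detect it with 80% power. If so, the power claimed for the primary endpoint is wrong on the plan's own figures. A trial with a true effect of the planned size would then miss significance more than four times in ten. A non-significant result could be read as fair evidence against deferred stenting, because the article describes the trial as having 80% power for an effect that it calls conservative.

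**Working it through.** **Inputs** (Sample size section): p1 = 0.229; 35% relative decrease, so p2 = 0.229 × 0.65 = 0.14885; difference 0.08015; two-sided alpha 0.05 (z = 1.960); 80% power (z = 0.8416); 10% loss; 1:1 allocation.

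**Attempt to reproduce 240 per arm.** Pooled two-proportion formula, with mean rate p̄ = (0.229 + 0.14885)/2 = 0.1889:

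n = [1.960 √(2 p̄(1 − p̄)) + 0.8416 √(p1(1 − p1) + p2(1 − p2))]² / (p1 − p2)²

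- First term: 1.960 × √(2 × 0.1889 × 0.8111) = 1.0850
- Second term: 0.8416 × √(0.1766 + 0.1267) = 0.4635
- n = (1.0850 + 0.4635)² / 0.08015² = 373.3, rounded up to 374 evaluable per arm
- With 10% loss: 374 / 0.9 = 415.6, so 416 enrolled per arm (832 in total)

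The plan has 240 enrolled per arm, a shortfall of 176 per arm.

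**Other methods on the same rates**

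| Method | Evaluable per arm | Enrolled per arm |
|---|---|---|
| Unpooled variance, two-sided | 371 | 413 |
| Arcsine, two-sided | 371 | 413 |
| Continuity correction, two-sided | 398 | 443 |
| Pooled, one-sided 5% (contradicts the text) | 294 | 327 |

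Two-sided event-based methods (Schoenfeld, Freedman) give about 406 to 515 enrolled per arm. None comes near 240.

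**Power of the plan as written.** Evaluable per arm: 240 × 0.9 = 216.

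Power = Φ{[0.08015 √n − 1.0850] / √(0.1766 + 0.1267)}

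- n = 216: Φ(0.169) = 56.7%
- n = 240 (no loss at all): Φ(0.284) = 61.2%
- Checks at n = 216: unpooled formula 57.1%; exact enumeration of the chi-squared test 57.2%; with Yates correction 51.9%; pooled formula, one-sided 5%, 68.6%

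**What 216 per arm can detect with 80% power**

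- From 22.9%: a relative risk of 0.551, i.e. 0.229 × 0.551 = 12.6%, a reduction of about 45%
- For a 35% reduction: a control rate of about 34.7%

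**Changes of input that come close to 240**

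- 22.9% as the deferred-arm rate: control 0.229 / 0.65 = 35.2%; 212 evaluable, 236 enrolled; power at 216 is 80.8%
- A relative decrease of 45% instead of 35%: 215 evaluable, 239 enrolled
- 35% used by mistake as the second proportion (22.9% vs 35%): 220 evaluable, 220 / 0.9 = 244.4, so 245 enrolled

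Each of these departs from the plain reading of the section.

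**Time scale.** The section calls 22.9% an annual rate, but the primary endpoint is at 30 days. In the same population the 30-day rate cannot exceed the annual one. The article gives no 30-day rate. Purely as assumptions, with 216 per arm and a 35% reduction, control rates of 20%, 15% and 10% give power of about 50%, 38% and 26%.

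**The case against.** The strongest defence is that the section never says which arm has the 22.9%. If it is the deferred-arm rate, the control rate is 35.2%, 240 per arm is about right, and the defect is only an unstated control rate. That is arithmetically sound, so the 57% is conditional on a reading. But the other reading is the natural one: the 22.9% is drawn from earlier observational data and a decrease is then applied to it. The 35.2% appears nowhere and is not justified, so the paragraph needs correcting in either case.

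A second objection is that restating the power as 57% would carry forward an annual rate for a 30-day endpoint. This stands, and it shapes the fix. It does not rescue the 80%, because on the plain reading a lower 30-day rate reduces power further.

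Third, the shortfall does not show that a 35% reduction is clinically optimistic; that rests on a cited study and centre experience not available here. The article also already plans odds ratios with 95% confidence intervals, which limits the risk of a null result being over-read. Both points are fair. Neither bears on whether the stated power follows from the stated inputs.

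**Conclusion.** The concern holds. On the stated inputs the required enrolment is about 416 per arm against 240 planned, and the planned size gives about 57% power against 80% claimed. The gap is far too large for rounding or the choice of formula to explain. The result assumes that 22.9% is the immediate-stenting rate, that 10% loss leaves 216 evaluable per arm, and that the primary comparison is a two-sided test of two proportions. Because 22.9% is labelled annual and the endpoint is at 30 days, 57% is a ceiling under that reading. If 22.9% was meant for the deferred arm, power would be about 81%, but only with a 35.2% control rate that the article neither states nor supports.

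**What to change.** Rewrite the Sample size paragraph so that the number follows from the inputs.

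1. State the assumed event rate in each arm, on the 30-day scale of the primary endpoint, and the source of the immediate-stenting rate.
2. Give the formula and the power that 480 patients (432 evaluable) provide for those rates. If 22.9% is kept as the immediate-stenting rate, say that power is about 57% for 22.9% against 14.9%, and that 80% power is reached only for a relative reduction of about 45% (to 12.6%). If the 30-day rate is lower, report the correspondingly lower power.
3. If 22.9% was meant as the deferred-arm rate, say so, state the 35.2% control rate and justify it at 30 days.

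Dropping the description of the effect as conservative, and saying that a non-significant result will be interpreted through its confidence interval, would be sensible but optional additions.

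The cost is wording in the protocol and analysis plan. No extra patients and no change in conduct are needed. The price is a less favourable power statement. Restoring 80% power on the stated inputs would instead need about 832 patients; that is a separate decision for the sponsor.
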